### Monitoring

Personnel not involved in this study will perform monitoring according to a pre-specified manual. In short, the monitors will control whether informed consent forms from all participating patients and practices are correctly filled out and signed. For a randomly chosen 15% sample, the SDM process with the application of the arriba-PPI tool will be monitored. At six months (T1), we will control in 15% of all patients whether they fulfilled the inclusion criteria before randomization. Furthermore, 15% of all data entered into SPSS will be checked by a second person not involved in the study.

### Sample size calculation

We based our sample size calculation on our primary endpoint. According to data of the statutory health insurance AOK Hessen, the average DDD of all PPI prescriptions per GP practice (averaged across all GP practices) accounts to 8244.47 per quarter with a standard deviation of 7850.89 (variation coefficient 0.95). This value is based on an average number of patients with PPI prescriptions of 56.20 per GP practice. Therefore, an average of DDD of PPIs of 146.7 per patient is assumed (8244.47/56.2). Taking into account a variation coefficient of 0.95, the standard deviation is 139.7 DDD of PPIs on a patient level. We consider a reduction by 15% as relevant, which would correspond to a difference of 22 DDD (15% of 146.7) between the control and intervention groups at T1. According to the sample size calculator for cluster-randomized trials of the University of Aberdeen’s Health Services Research Unit [29], we will need 204 GP practices with 15 patients each if we want to prove such a difference with an intraclass correlation coefficient of 0.1 [30], a significance level of 0.05, and a power of 80%. The primary outcome relates to patient-level data. Thus, we adapted our calculation to the cluster structure (patients in GP practices). The number of practices refers to the number that needs to be randomized. To cover for drop-out practices after randomization, we increased the number of practices to be recruited to 210. In addition, patients might leave the study at their own request after inclusion in the study but before receiving the actual intervention. We decided to have a buffer considering non-predictable dropouts. Therefore, each study practice is required to recruit at least 15 patients but not more than 25 patients, as differences in cluster size can have a negative influence on intracluster variability. Practices will include patients in the study according to the chronological order in which the patients signaled their willingness to participate in the study. By setting this range of patients, the probability that the number of patients per practice varies only minimally increases. If 15 potential study patients cannot be enrolled in the study within the timeframe for recruitment, the study practice and its recruited study patients will still be included in the analysis.

### Data management and statistical analysis

Data will be recorded into SPSS at each study center and transferred to the blinded trial statistician. We will use intention-to-treat and per-protocol analyses. The primary outcome will be analyzed by multilevel analyses with the statistical program R following intention-to-treat principles [31]. These analyses take into account the clustering of patients by practices and allow for different modelling of predictors, e.g. group affiliation as fixed and/or random effect. Furthermore, these analyses allow adjustment for variables which showed differences between the intervention and control groups despite randomization and which are considered to be of prognostic importance. In case of missing variables, suitable imputation methods will be used [32]. We will perform sensitivity analyses (worst case, best case, complete case) in order to check for the influence of missing data on the results.

The evaluation for the secondary outcomes will also be done by multilevel analyses by adopting covariates on patient and/or cluster level. Elaborated evaluations in multivariate procedures allow a more detailed analysis of prescription behavior. All statistical tests will be two-tailed and an alpha of 5% will be used throughout. Besides statistical significance, effect sizes will also be evaluated [33].

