### Trial design and setting

The arriba-PPI trial is a national multicenter cluster-randomized controlled trial with an observation period of one year to reduce long-term prescription of PPIs. It will be conducted in Germany in the mid- and north Hessia and Westphalia-Lippe regions. Three study centers will be involved: the Institute of General Practice of Marburg University; Institute of General Practice of Heinrich-Heine-University Düsseldorf; and Institute of General Practice and Family Medicine of Witten/Herdecke University. The arriba-PPI trial will be located in the primary care setting. Details on the study procedure are outlined in Fig. 1.

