### Randomization

The GP practice is regarded as the unit of randomization. Each participating GP practice with the recruited patients will be randomized to either having access to the arriba-PPI tool (intervention) or not and performing care as usual (control). We decided to apply cluster randomization in order to avoid contamination if the GP would use the tool for some patients but not for others as we expect that a learning effect will take place. After completion of patient recruitment, the GP practice will notify the corresponding study center providing the number of patients recruited. The practice will then be randomized using computerized sequence generation with a simple randomization scheme generated by the random package of the program R [28]. Randomization will be stratified by study center. Randomization lists will be kept closed. To assure concealment of allocation, no patients can be included once recruitment is completed and randomization has been performed.

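### Randomization is stratified by study center, but the primary model names only practices and its one stated ground for adjustment is an observed arm difference, which a balanced stratum would not meet

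*Protocol article*

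**What the plan says.** Under Trial design and setting: "Three study centers will be involved". Under Randomization, the practice is the unit, "Randomization will be stratified by study center", and the practice is allocated "using computerized sequence generation with a simple randomization scheme generated by the random package" of R. No blocks are mentioned, and center is the only stratum named.

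Under Data management and statistical analysis, the primary outcome is to be analyzed by multilevel models, and "These analyses take into account the clustering of patients by practices". Center is not named. The same paragraph says that these models permit "adjustment for variables which showed differences between the intervention and control groups despite randomization and which are considered to be of prognostic importance". No other ground for adjusting the primary comparison is given.

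For the secondary outcomes the section speaks of covariates at the level of the patient or the cluster, without the condition of an observed difference. On testing it says "All statistical tests will be two-tailed and an alpha of 5% will be used throughout".

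**The concern.** A factor used to stratify the randomization belongs in the analysis because of the design, not because of what the data show. The stated ground for adjustment works the other way. Stratification is meant to stop center from differing between arms, so the better it works, the less center qualifies. If center does differ by chance, it would enter the model only after the imbalance had been seen, and the form of the primary model would then depend on the allocation that happened to occur.

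At stake is mainly precision. Lists drawn by simple randomization within each center do not force balance, so stratifying in that way gains precision only if center is also in the model. If the lists were in fact blocked, the model would report a standard error that still contains center variation which the design had removed from the treatment contrast.

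**Working it through.** **Inputs from the article (Sample size calculation).** Difference 22 DDD; patient-level SD 139.7 DDD; ICC 0.1; 15 patients per practice; 204 practices; "a significance level of 0.05, and a power of 80"%.

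**Assumptions, not in the article.** Center accounts for a share s of the between-practice variance, varied from 0 to 30%. The three centers are of equal size (68 practices each). The total between-practice variance stays at 0.1 SD².

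**1. The plan's own figure.** Without clustering, 633 patients per arm are needed. The design effect is 1 + (15 − 1) × 0.1 = 2.4. Then 633 × 2.4 = 1519.2 patients per arm, and 1519.2 / 15 = 101.28, rounded up to 102 practices per arm, or 204 in all. The stated figure is reproduced. Power at 204 practices is 80.3%.

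**2. Standard error without center.** The variance of a practice mean is 0.1 + 0.9/15 = 0.16 SD². With 102 practices per arm, SE = 139.7 × √(0.16 × 2/102) = 7.82 DDD.

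**3. What center can remove.** With center in the model and balanced arms, the variance is 0.16 − 0.1s. The ratio of the SE with center to the SE without it is √((0.16 − 0.1s)/0.16):
- s = 5%: √(0.155/0.16) = 0.984
- s = 10%: √(0.15/0.16) = 0.968
- s = 30%: √(0.13/0.16) = 0.901

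**4. Simple allocation within center (the article's wording).** Simulation of practice means, 8000 trials per setting:

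| Center share s | Type I error without center | Mean SE without / with center (DDD) | Power at 22 DDD without / with center |
|---|---|---|---|
| 0 | 0.050 | 7.83 / 7.87 | 79.5% / 79.3% |
| 5% | 0.047 | 7.83 / 7.75 | 80.5% / 81.3% |
| 10% | 0.050 | 7.84 / 7.63 | 80.0% / 82.3% |
| 20% | 0.051 | 7.83 / 7.36 | 78.6% / 83.9% |
| 30% | 0.051 | 7.83 / 7.10 | 79.6% / 86.7% |

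The Monte Carlo error of a power near 80% is √(0.8 × 0.2/8000), about 0.45 percentage points, so the differences at s = 0 and s = 5% are small against the noise. The type I error stays near 5% without center.

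**5. Blocked allocation within center (only if blocks were used).** Leaving center out overstates the SE by 1/0.968 − 1 = 3% at s = 10% and by 1/0.901 − 1 = 11% at s = 30%. The true test size is 2 × (1 − Φ(1.96/ratio)), which gives 4.3% and 3.0%; the simulation gives 4.7% and 2.8%. Simulated power without and with center is 80.5% and 82.2% at s = 10%, and 82.2% and 87.6% at s = 30%.

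**6. Cost.** At the level of practice means, the residual degrees of freedom fall from 204 − 2 = 202 to 204 − 4 = 200. If centers do not differ, power is about 80% either way under blocked allocation and about 79% either way under simple allocation.

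**The case against.** The strongest case against the point is that the analysis section only says what multilevel models permit. It nowhere says that other variables are excluded, and the article condenses a fuller plan that may list center. This stands in part. A reader might infer that the rule shuts center out, but the wording is permissive and does not support that. What remains is that the article states one ground for adjustment, and it is the wrong ground for a stratification factor. That is a poorly fixed rule, not just a detail left to a later document.

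A reader might also infer that the confidence intervals will be too wide and the test conservative. That needs balance forced within center. The article describes a simple scheme and mentions no blocks, so the better-supported consequence is lost precision with the type I error intact. Under simple allocation a chance imbalance in center, if judged prognostic, would also meet the stated condition. Center could therefore enter, though only after the imbalance had been seen.

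The objection also holds for the secondary outcomes: their wording already admits a practice-level covariate such as center.

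Finally, the size is assumed. A 30% share implies a between-center SD of √0.03 × 139.7 = 24 DDD, larger than the 22 DDD target, and nothing in the article supports or excludes this. The sample size took no credit for stratification, so omitting center does not bring power materially below plan.

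**Conclusion.** The point holds as a weakness in how the primary model is fixed. The randomization has a stratum that the described model does not name, and the stated ground for adjustment would pass over that stratum when it is balanced, or admit it only after an imbalance is seen. It is not a threat to validity: in no setting examined is the type I error materially above 5%, and power without center stays at about 79% to 82%, close to the planned 80%.

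What is given up is precision that could be had at almost no cost. At an assumed center share of 10% to 30% of the between-practice variance, power with center is about 82% to 88%. Below a share of about 5% the gain is negligible. These figures rest on the assumed share, equal centers, and the article's own SD, ICC and cluster size. An overstated SE and a test size of 4.3% to 3.0% would apply only if allocation was in fact blocked within center.

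**What to change.** State that study center (three levels) enters the primary model as a fixed effect regardless of observed balance, and that the condition of an observed arm difference ("adjustment for variables which showed differences between the intervention and control groups despite randomization") does not apply to it. Use the same term in the secondary models for consistency; their wording already allows it.

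The cost is a sentence in the analysis text and two of about 200 degrees of freedom. Center is known for every practice, so no new data are needed, and the sample size of 204 practices does not change.

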**Methods:**

The arriba-PPI tool is an electronic decision support system that supports shared decision-making and evidence-based decisions around the long-term use of PPIs at the point of care. The tool will be evaluated in a cluster-randomized controlled trial involving 210 GP practices and 3150 patients in Germany. GP practices will be asked to recruit 20 patients aged ≥ 18 years regularly taking PPIs for ≥ 6 months. After completion of patient recruitment, each GP practice with enrolled patients will be cluster-randomized. Intervention GP practices will get access to the software arriba-PPI, whereas control GPs will treat their patients as usual. After an observation period of six months, GP practices will be compared regarding the reduction of cumulated defined daily doses of PPI prescriptions per patient.

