### Measurements

The primary endpoint is the cumulated DDDs of PPIs per study patient at six months (T1). Secondary endpoints are the proportion of PPI patients in the practice during the six months after allocation (T1), the cumulated DDDs of PPIs per study patient during the 12 months after allocation (T2), the proportion of PPI patients in a practice during the time span of 6–12 months after allocation (T2), and the average accumulated total DDDs of PPIs in a practice for all patients during the time span of 6–12 months after allocation (T2).

For outcome measurement, information on PPI prescription (substance, dose, package size) per patient will be recorded from the practice software for a time span of six months before T0 to 12-month follow-up. Furthermore, the number of all patients taking PPIs per practice and the number of patients per practice will be assessed for the time span of T0 to 12 months after allocation (Fig. 2).

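### Covariate adjustment of the primary analysis is tied to observed imbalance between arms, instead of prespecifying the pre-T0 DDD that is already collected

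*Protocol article*

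**What the plan says.** Protocol article, Data management and statistical analysis: "The primary outcome will be analyzed by multilevel analyses with the statistical program R following intention-to-treat principles". No covariate is named for that model. The one sentence on adjustment says that "these analyses allow adjustment for variables which showed differences between the intervention and control groups despite randomization" and continues "and which are considered to be of prognostic importance". The two conditions are joined, so a variable has to meet both.

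Protocol article, Measurements: the primary endpoint is each study patient's cumulated DDD of PPIs at six months (T1). Prescription details (substance, dose, package size) "per patient will be recorded from the practice software for a time span of six months before T0 to 12-month follow-up". The same quantity is therefore available for every patient over an equally long period before T0, from the same source.

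Protocol article, Randomization: practices are randomized with stratification by study center. Sample size calculation: the target of 204 practices uses no baseline correlation.

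**The concern.** Under sound randomization, any baseline difference between arms is due to chance. A covariate improves the estimate to the extent that it predicts the outcome, and it does so whether or not the arms differ on it. The second condition in the plan, prognostic importance, is the right criterion. The first condition undermines it, because a variable that strongly predicts six-month DDD does not qualify if the arms happen to be balanced.

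Two things are at stake. First, the content of the primary model is settled only after the arms have been compared, so the primary estimate depends on a data-driven choice. Second, precision is lost in exactly the situation where the rule does not apply. The natural candidate, the patient's own DDD in the six months before T0, costs nothing to include because it is already recorded.

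**Working it through.** **Inputs** (Protocol article, Sample size calculation, unless noted): difference 22 DDD; patient-level SD 139.7; ICC 0.1; 15 patients per practice; 204 practices; power 80%; two-sided alpha 0.05 (Data management and statistical analysis). Assumed here: equal allocation, 102 practices per arm, as the ratio is not stated; and the correlation r between pre-T0 and six-month DDD, which the article does not give.

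**Step 1: reproduce the plan's figure.**
- Patients per arm without clustering: 2 × [139.7 × (1.960 + 0.842) / 22]² = 633.
- Design effect: 1 + (15 − 1) × 0.1 = 2.4.
- Practices per arm: 633 × 2.4 / 15 = 101.3, rounded up to 102, so 204 in total. This matches the plan.
- SE of the difference: 139.7 × √(2 × 2.4 / (102 × 15)) = 7.82 DDD.
- Power: Φ(22 / 7.82 − 1.96) = 80.3% (79.9% with the t distribution).

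**Step 2: add pre-T0 DDD as a covariate, with the same r at patient and practice level.** The variance is multiplied by 1 − r².

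| Assumed r | Variance factor | SE (DDD) | Power at 204 practices | Practices for 80% |
|---|---|---|---|---|
| 0 | 1.00 | 7.82 | 80.3% | 204 |
| 0.3 | 0.91 | 7.46 | 83.8% | 186 |
| 0.5 | 0.75 | 6.78 | 90.1% | 152 |
| 0.7 | 0.51 | 5.59 | 97.6% | 104 |

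**Step 3: a more cautious case, where baseline explains only within-practice variance.** In units of the total variance, a practice mean has variance 0.1 + 0.9/15 = 0.16. Reducing only the second term gives 0.1 + 0.06 × (1 − r²).
- r = 0.3: 0.1546 / 0.16 = 0.966, power 81.6%.
- r = 0.5: 0.1450 / 0.16 = 0.906, power 84.0%.
- r = 0.7: 0.1306 / 0.16 = 0.816, power 87.5%.

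**Step 4: how the two levels combine.** If baseline DDD has the same ICC of 0.1, the correlation between practice means is (0.1 / 0.16) × r at practice level + (0.06 / 0.16) × r at patient level, that is, weights of 0.625 and 0.375. The practice-level correlation carries most of the gain. With a practice-level correlation of zero and 0.5 at patient level, r = 0.375 × 0.5 = 0.1875. The variance factor is then 1 − 0.1875² = 0.965, the SE is 7.82 × √0.965 = 7.69 and power is Φ(22 / 7.69 − 1.96), about 82%. The Step 3 figures are therefore cautious but not a floor.

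**The case against.** **The wording is permissive.** The plan says that multilevel models allow such adjustment. It does not say that adjustment is confined to imbalanced variables, and it does not rule out pre-T0 DDD. A reader might infer that the primary model will certainly omit baseline DDD. The text does not support that: this is a journal article, and a separate analysis plan could fix the covariates. This objection stands as far as the missing covariate list goes. It does not cover the imbalance condition, which is stated in the article and is a poor criterion wherever it is applied.

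**Prognosis is part of the rule.** It would be wrong to describe the rule as based on imbalance alone. The prognostic condition limits arbitrary selection, but because both conditions must hold it does not remove the problem.

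**The unadjusted analysis is valid and powered.** Randomization protects the unadjusted comparison, and the stated 80% is reproduced. The statistician is to be blinded (Blinding), which limits steering toward one arm. Both points stand and lower the severity. Blinding neither fixes the model in advance nor recovers precision.

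**The gain is unknown.** The article gives no r. Restricting entry to regular users of at least six months and excluding as-required use (Inclusion and exclusion criteria) may narrow the baseline range and lower r. This also stands, which is why only a range is given.

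**Change score against follow-up value.** The abstract says that "GP practices will be compared regarding the reduction of cumulated defined daily doses of PPI prescriptions per patient", and a reader might infer that a change score competes with the endpoint in Measurements. The article does not support this. Table 1, Measurements and the sample size calculation all refer to DDD at six months or T1, and the objectives use a reduction to mean a contrast with usual care. No change score is defined anywhere.

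**Conclusion.** The point holds as an improvement that should be made, not as a flaw that threatens the trial. The only covariate rule stated for the primary analysis makes observed imbalance a condition of adjustment, and no part of the article makes the collected pre-T0 DDD a covariate.

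On the planning inputs, prespecifying it would raise power from about 80% to between 84% and 98% for an assumed r of 0.3 to 0.7 at both levels. If only within-practice variance is explained, the range is about 82% to 88%. These figures rest on an assumed correlation, equal allocation, 15 patients in every practice and the plan's SD and ICC. The planning SD is taken from quarterly figures while the endpoint covers six months; that is a separate matter and does not alter the variance factor 1 − r².

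A reader might conclude that the trial is underpowered or its primary test invalid. Neither follows.

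**What to change.** Delete the condition that the arms must differ, and name the covariates before any comparison of arms. Suggested primary model: six-month post-allocation DDD per patient, with fixed effects for arm, the patient's DDD in the six months before T0 and study center (the stratification factor), and a random intercept for practice. Adding the practice mean of pre-T0 DDD is optional but worthwhile, because the relation with outcome may differ between patient and practice level. Any further prognostic covariates should be listed by name; adjustment for variables found to be imbalanced can be kept as a labelled sensitivity analysis.

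The cost is one or two sentences in the protocol or analysis plan. No new data are needed and the sample size can stay as it is.

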### Qualitative sub-study

In order to explore the experiences of the usage of the arriba-PPI tool, the adoption of the advice, and the SDM process, we will conduct in-depth interviews with participating GPs and patients. Therefore, we will invite randomly selected GPs and patients to separate focus group meetings or individual interviews. Interviews will be conducted by means of a semi-structured interview guideline, recorded, anonymized, and transcribed verbatim. The qualitative text will be analyzed by thematic qualitative text analysis in multidisciplinary groups.

